#### The VR psychological treatment

The treatment being tested is Phoenix VR self-confidence therapy, which is a VR application recommended for adults (16+) attending psychosis services who have low levels of positive self-beliefs. This software is intended to increase positive self-beliefs. The treatment was designed by our team at the University of Oxford, with young people with lived experience taking part in the design process. The treatment was programmed by the University of Oxford. Phoenix is a UKCA marked, class I medical device (standalone software as a medical device). The Phoenix software application is composed of a set of virtual environments, including different scenes created using three-dimensional (3D) models, ambient audio and 3D virtual characters, with animations and speech. The environments are driven by source code which handles the logic of the programme, the behaviour of the computer characters, as well as the user interaction and data storage. The software is built using Unity (Unity Technologies). Unity acts as a render engine, displaying the virtual environments to the user through the headset. The application runs through the Unity software application on a Meta Quest 2 VR Headset.

The primary treatment goal is to help young people who have been given a diagnosis of schizophrenia (or related condition) to increase their psychological well-being by building up positive self-beliefs. Patients can keep the headset for 6 weeks in order to use Phoenix on their own. The treatment is supported by a staff member over six sessions. In the first meeting, the staff member introduces Phoenix and helps the person try it out. The staff member also helps the person set real-world goals and between-session tasks to improve confidence and reviews progress. VR does not need to be used in the subsequent in-person meetings since the patient is able to use it at home but most sessions to date have included approximately twenty minutes within VR. Phoenix is used to spark positive self-beliefs that are then consolidated via real-world activities.

The six key mechanisms of action within Phoenix are to: build vivid memories of successful and rewarding interactions; help identify strengths; learn to tolerate fearful emotions and still succeed; learn to appraise situations more positively and with more self-kindness; develop the ability to savour positive experiences and connect with other people; and increase engagement in meaningful activities. Phoenix has three main therapeutic areas within VR for the user: creating a sense of achievement and mastery to develop the belief ‘I can make a difference’; succeeding in challenging situations to develop the belief ‘I can do this’; and engaging in pleasurable activities to develop the belief ‘I can enjoy things’. The achievement and mastery scenario is set in a community garden, with ten tasks relating to the care of plants, animals and a farmhouse. Each task is broken down into several steps for the participant to complete. For example, caring for plants includes preparing the soil, planting seeds, watering and picking the crops. The challenging situation is a TV studio, with the user having to speak to camera in front of an audience. Patients read out a weather forecast presented on an autocue. There are 10 levels of difficulty, varying in the size of the audience, the difficulty of the speaking task, and the environment itself (eg, gradual introduction of cameras and spotlights). The pleasurable experiences are set near a lake by a forest and tasks include relaxation exercises (eg, savouring, progressive muscle relaxation) and games (eg, a throwing game, playing on a drum set). A virtual coach (called Farah) guides the participant in the best way to think, feel and respond. Farah provides instruction, encouragement and positive reinforcement. Farah first meets users in her glass-fronted office that overlooks mountains and provides instructions throughout the programme. Users choose which VR scenarios they wish to complete and can repeat activities as often as they would like.

#### Control condition

Participants who are allocated to the control arm will continue to receive their usual care. No additional interventions will be offered by the research team. Treatment as usual for the participants within this trial will typically consist of prescription of psychiatric medications and meetings with a mental health practitioner. Treatment as usual will vary across individuals. We will collect detailed data on treatment as usual.

#### Adverse events

A trial standard operational procedure has been written for adverse events. We will record the occurrence of any serious adverse events (SAE) reported to us and also check each patient’s medical notes at the end of their participation in the trial. An adverse event is defined by the ISO14155:2011 guidelines for medical device trials as serious if it: (A) results in death, (B) is a life-threatening illness or injury, (C) requires hospitalisation or prolongation of existing hospitalisation, (D) results in persistent or significant disability or incapacity, (E) medical or surgical intervention is required to prevent any of the above, (F) leads to foetal distress, foetal death or consists of a congenital anomaly or birth defect or (G) is otherwise considered medically significant by the investigator.

Life-threatening in the definition of an SAE refers to an event in which the subject was at risk of death at the time of the event; it does not refer to an event that hypothetically might have caused death if it were more severe. A planned hospitalisation for a pre-existing condition, without a serious deterioration in health, is not considered to be an SAE.

The sorts of SAEs that can typically happen to this participant group include: deaths, suicide attempts, serious violent incidents and admissions to hospital. SAEs are recorded using an SAE report form. The relationship between the investigational medical device or other research procedure and the occurrence of each SAE will be assessed and categorised. The investigators will use clinical judgement to determine the relationship (including whether the patient reports a link to the study). Alternative causes, such as natural history of the participant’s underlying condition, concomitant therapy, other risk factors, etc, will be considered. The study team will make an initial assessment of whether the SAE is potentially related to the device or trial procedures and report to the regulatory authorities within the appropriate timescales. The decision about relatedness will be reviewed by the DMEC chair in the first instance.

We will also record adverse events that are not serious. This would include any adverse device effects from the VR treatment, including those resulting from insufficient or inadequate instructions for use, deployment, installation or operation, or any malfunction of the software. It also includes any event resulting from user error or intentional misuse.

#### Analysis

A full-statistical analysis plan will be approved before any analysis. We will report data in line with the CONSORT (Consolidated Standards of Reporting Trials) 2010 statement^36^ showing attrition rates and loss to follow-up. The primary analyses will be carried out using the intention-to-treat principle. That is, after randomisation, participants will be analysed according to their allocated intervention arm irrespective of what intervention they actually receive, and with data available from all participants included in the analysis including those who do not complete therapy. The outcome analyses will be conducted by statisticians in the University of Oxford Primary Care Clinical Trials Unit.

Baseline variables will be presented by randomised group using frequencies (with percentages) for binary and categorical variables and means (and SD) or medians (with lower and upper quartiles) for continuous variables, along with minimum and maximum values and counts of missing values. There will be no tests of statistical significance nor confidence intervals for differences between groups on any baseline variables. There will be no planned interim analysis for efficacy or futility on the primary outcome.

We will test the primary hypothesis for between-group difference in the primary outcome using a linear mixed effects model which models the response at 6 weeks and 12 weeks, with baseline outcome measure and treatment assignment as fixed effects, with a patient specific random intercept. An interaction between time and randomised group will be fitted as a fixed effect to allow estimation of treatment effect at all time points. The linear mixed effects model will account for missing data assuming data are missing-at-random. Standard residual diagnostics will be assessed for the appropriateness of the model. A p<0.05 will be used as the level of statistical significance. Similar mixed effect models will be used to analyse secondary outcomes. Treatment differences estimated from linear mixed effects models will additionally be reported as standardised mean differences (mean group difference divided by whole group SD at baseline).

The sample size of 80 patients takes into consideration a maximum attrition rate of 10% and provides 80% power to detect a moderate difference (d=0.67) in positive self-beliefs, from randomisation to 6 weeks at a 5% level of significance using an independent groups t-test (two sided). Further power is likely to be gained by use of mixed-effects models.

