**Methods and analysis:**

80 patients with psychosis, aged between 16 and 30 years old and with low levels of positive self-beliefs, will be recruited from National Health Service (NHS) secondary care services. They will be randomised (1:1) to the Phoenix VR self-confidence therapy added to treatment as usual or treatment as usual. Assessments will be conducted at 0, 6 (post-treatment) and 12 weeks by a researcher blind to allocation. The primary outcome is positive self-beliefs at 6 weeks rated with the Oxford Positive Self Scale. The secondary outcomes are psychiatric symptoms, activity levels and quality of life. All main analyses will be intention to treat.

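### A random intercept alone ties the 6-week primary standard error to the 12-week variance; a visit-specific covariance would remove this conditional risk cheaply

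*Protocol article*

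**What the plan says.** The Abstract fixes the endpoint at one time: "The primary outcome is positive self-beliefs at 6 weeks rated with the Oxford Positive Self Scale". The Analysis section tests it with a "linear mixed effects model which models the response at 6 weeks and 12 weeks", listing "baseline outcome measure and treatment assignment as fixed effects, with a patient specific random intercept". It continues: "An interaction between time and randomised group will be fitted as a fixed effect to allow estimation of treatment effect at all time points". The 6-week effect is therefore a contrast of its own within a two-visit model.

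The random intercept is the only covariance term named. On significance: "A p<0.05 will be used as the level of statistical significance". On checking: "Standard residual diagnostics will be assessed for the appropriateness of the model". No alternative covariance is named in case the check fails. The section also says "A full-statistical analysis plan will be approved before any analysis". That plan is not available here.

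The sample size comes from a two-sided independent-groups t-test at 6 weeks, and the article adds: "Further power is likely to be gained by use of mixed-effects models".

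**The concern.** With two post-baseline visits and a homoscedastic residual, a random intercept is compound symmetry: one variance shared by both visits and one correlation between them. The primary question concerns 6 weeks only, yet its standard error then depends on how variable patients are at 12 weeks.

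If the 12-week residual variance is the larger, the 6-week standard error is too big, and the test is conservative and loses some power. If it is the smaller, the standard error is too small and the false-positive rate exceeds 5%. The trial does not need this restriction, because two visits can carry their own variances at the price of one parameter.

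Some widening is plausible. The model adjusts for baseline, so the relevant spread is what remains after that adjustment. If scores correlate less with baseline at 12 weeks than at 6, r exceeds 1 even when the raw SDs are equal.

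**Working it through.** **1. The plan's own figure.** Inputs from the Analysis section: d = 0.67, 80% power, two-sided 5% t-test, 80 randomised 1:1, attrition up to 10%. Noncentral-t power is 80.05% with 36 per arm and 78.9% with 35. So 2 × 36 = 72, and 72/0.9 = 80. The stated sample size reproduces.

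**2. Effect of the common variance.** With complete data, the model's variance for the 6-week contrast uses the average of the two visits' residual variances. Relative to the correct standard error:

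- f = sqrt((1 + r²)/2)
- size = 2 × [1 − Φ(1.96 f)]
- power = Φ(0.67 × sqrt(36/2) − 1.96 f), with no gain from baseline adjustment

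Example, r = 1.2: f = sqrt((1 + 1.44)/2) = 1.105, size = 3.0%, power = Φ(2.843 − 2.165) = 75%.

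**3. Plausible values of r.** The article gives none. Suppose the raw SDs are equal and the correlations with baseline are ρ6 and ρ12. Then r = sqrt((1 − ρ12²)/(1 − ρ6²)). All correlations here are assumptions.

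| ρ6, ρ12 | r | f | size |
|---|---|---|---|
| 0.5, 0.4 | sqrt(0.84/0.75) = 1.06 | 1.030 | 4.4% |
| 0.6, 0.5 | sqrt(0.75/0.64) = 1.08 | 1.042 | 4.1% |
| 0.6, 0.4 | sqrt(0.84/0.64) = 1.15 | 1.075 | 3.5% |
| 0.7, 0.5 | sqrt(0.75/0.51) = 1.21 | 1.111 | 2.9% |

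**4. Simulation of the stated model.** The random-intercept model was fitted by REML with 80 patients and about 10% missing at each visit. Assumed correlations were 0.5 with baseline at both visits and 0.7 between follow-ups. The 12-week score was scaled by r, and the effect was 0.67 of the 6-week SD. There were 8,000 null runs and 3,000 power runs per value of r. The comparator was a 6-week-only ANCOVA, whose variance comes from 6 weeks alone; it stands in for a visit-specific covariance.

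| r | f | formula size | simulated size | formula power, no baseline gain | simulated power | ANCOVA size | ANCOVA power |
|---|---|---|---|---|---|---|---|
| 0.8 | 0.906 | 7.6% | 8.2% | 86% | 94% | 5.6% | 90% |
| 0.9 | 0.951 | 6.2% | 6.1% | 84% | 91% | 5.2% | 90% |
| 1.0 | 1.000 | 5.0% | 5.0% | 81% | 90% | 5.1% | 89% |
| 1.1 | 1.051 | 3.9% | 4.0% | 78% | 88% | 5.1% | 89% |
| 1.2 | 1.105 | 3.0% | 3.2% | 75% | 84% | 4.9% | 89% |
| 1.3 | 1.160 | 2.3% | 2.3% | 72% | 83% | 5.0% | 89% |
| 1.5 | 1.275 | 1.3% | 1.3% | 63% | 75% | 4.9% | 90% |

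Monte Carlo standard errors are about 0.2 to 0.3 points for size and under 1 point for power. Simulated size follows the formula. The power cost against a 6-week variance is about 1 point at r = 1.1 and 4 to 5 points at r = 1.2. The formula power column omits baseline adjustment, which the stated model includes, so it understates that model's power whenever baseline is predictive.

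**The case against.** The best defence is that nothing has been shown to go wrong. The documents give no SD at 6 or 12 weeks. The test has its nominal size at r = 1 and stays between about 4% and 6% for r from 0.9 to 1.1. A random intercept does not by itself rule out visit-specific residual variances, the unseen analysis plan may set them, and residual diagnostics are planned. A baseline-adjusted random-intercept model is a standard choice.

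Most of this stands, and it limits the point to a conditional one. Two parts do not dispose of it. The random intercept is a stated choice and not a detail left open. The diagnostics carry no stated consequence, and acting on them would mean altering the primary model after seeing outcome data.

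Four stronger readings might be inferred, and the documents do not support them:

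- *The primary test is mis-sized.* That requires unequal residual variances, which cannot be shown from the article. Inflation also requires a smaller 12-week variance, and nothing there suggests one.
- *The entry cut-off of 50 on the primary scale drives the problem.* The model conditions on baseline. Under a linear normal relation, truncating baseline leaves the variance given baseline unchanged. Fading correlation is what moves r.
- *The mixed model would lose power against the planned t-test.* Under the assumed correlations it has 83% at r = 1.3, against the t-test's 80%. A loss appears only at larger ratios (75% at r = 1.5).
- *Visit is omitted from the fixed effects.* A time-by-group interaction ordinarily brings its main effects with it in a condensed description.

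**Conclusion.** The point holds as a robustness weakness of modest size. It is not a demonstrated error. Read with a homoscedastic residual, the stated model lets the 12-week variance set part of the 6-week standard error.

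Conservatism is the likelier direction: for assumed r of about 1.05 to 1.2, size is about 3% to 4.5% and a few points of the mixed model's expected extra power are lost. Power at d = 0.67 stays above 80% up to r of about 1.3, given an assumed correlation of 0.5 with baseline. In the less likely direction, size is about 6% at r = 0.9 and about 8% at r = 0.8. Every value of r and every correlation is an assumption. The conclusion also depends on the unseen analysis plan not already allowing visit-specific variances.

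**What to change.** Before the analysis plan is approved:

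- Replace the patient random intercept with an unstructured 2×2 within-patient covariance for the 6- and 12-week scores. Letting the residual variance differ by visit would also do.
- List visit, arm, visit-by-arm, baseline and baseline-by-visit as the fixed effects, so that the baseline slope can differ between visits.
- Fit by REML with a small-sample degrees-of-freedom correction such as Kenward-Roger.
- Name the 6-week contrast as the primary test, and use the same form for the secondary outcomes analysed this way.

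The cost is a wording change, one extra variance parameter and one extra slope, with about 72 patients expected to contribute. No new data are needed. At r = 1, the 6-week ANCOVA used as a stand-in gave up nothing material (89% power against 90%).

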#### Ethics and dissemination

The trial has received Health Research Authority (HRA) approval (IRAS 312539). The trial received ethical approval from the NHS London—Harrow Research Ethics Committee (22/LO/0273). The results of the trial will be published in a peer-reviewed journal and made open access. Deidentified participant data will be available in anonymised form on reasonable request, subject to review and contract with the University of Oxford, following the publication of results.

#### Patient and public involvement

Patient and public involvement has been supported by the McPin Foundation, a charity that aims to put the lived experience perspective at the heart of mental health research. A patient advisory group (PAG), comprising young people who have been diagnosed with psychosis, has helped design the VR therapy, try prototypes and contributed to the development of the primary outcome measure.
